#### Quantitative analysis

This will primarily be completed on an intention-to-treat analysis. All quantitative data will be assessed for normality and analysed using appropriate parametric and non-parametric statistics (eg, within and between measures t-tests and analyses of variance); statistical significance will be set at p=0.05. Secondary per protocol analyses will be carried out.

A post hoc analysis will be carried out, which will exclude patients in either arm that received pulmonary rehabilitation as part of their usual care. We would anticipate that patients who participate within the study will not require pulmonary rehabilitation. However, due to pulmonary rehabilitation being a part of ‘best’ usual care, this will not be withheld from the patient.

Quantitative data for all outcomes will be transcribed from the case report form (CRF) onto an electronic database. A statistical software package will be used to carry out quantitative analyses. Predictive analytics software (SPSS; Statistical Package for the Social Sciences) will be used to analyse the data, the licence for which is provided by University Hospitals of Leicester NHS Trust. Continuous variables will be presented as mean and SD or median and IQR, and categorical data will be presented as frequencies and percentages. Data will be checked for normality and appropriate parametric and non-parametric tests will be used. Any baseline differences will be adjusted for. Any missing data will be imputed, and both intention-to-treat and per-protocol analyses will be conducted.

We have not secured funding for a healthcare utilisation analysis but would anticipate further CLAHRC (Collaboration and Leadership in Applied Health Research and Care) funding if the trial is clinically effective.

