Implementation focused work carried out following these studies with HCPs in primary care and local Clinical Commissioning Groups (CCGs), demonstrated considerable interest in delivering the SPACE for COPD(C) intervention as a group-based intervention rather than on a one-to-one basis. The most common theoretical rationale underpinning delivery of group-based self-management support interventions is Social Cognitive Theory/Social Learning Theory.^11 12^ Bandura’s (1977, 1997) social learning theory posits that behaviour is influenced by beliefs about one’s ability to perform a particular behaviour (self-efficacy expectations), beliefs about the effectiveness of the behaviour (eg, the advantages and disadvantages of performing this behaviour; outcome expectations) and learning through social observation (including social norms, social support or pressure and the behaviours of others). Peer support and use of other patients as role models are approaches grounded in this theory and directly applicable to group-based self-management support interventions.

Delivery of SPACE for COPD(C) as a group-based intervention allows for several face-to-face contacts between patients and HCPs over a number of sessions. These contacts could be spread out further across a longer period, which may be more successful in maintaining behaviour change. Furthermore, having earlier sessions closer together in time allows group cohesion to take place, an important factor in optimising group dynamics.^13^

The SPACE for COPD(C) intervention has also previously been delivered by a member of the research team rather than by existing clinical services. If the group-based intervention were to be implemented in primary care following the current study, importance would be placed on delivery by HCPs in a format that is feasible and acceptable to HCPs, health service providers and to patients. Understanding how this intervention can be delivered within existing health services and identifying key barriers and facilitators to its implementation is an important next step in the development of this complex intervention.

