### Randomisation

Once participants have consented to take part in the study and spirometry has confirmed a COPD diagnosis, participants are randomised by an unblinded member of the study team using an online randomisation tool (sealed envelope).^14^ Individuals are randomised (1:1) to the control group or the intervention (SPACE for COPD(C) group-based self-management programme) group. The system randomises patients in random permuted blocks. This allows for the 1:1 ratio, but due to the random permuted blocks of 2, 4 or 6 ensures full randomisation. Simple randomisation has been chosen as there has been no requirement to stratify by age, gender, location or other variables. Participants are immediately informed of their allocated treatment by an unblinded member of the study team. Unblinding is permissible in the case of medical emergencies (eg, cardiac arrest) or patients being admitted to hospital for an exacerbation.

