#### SPACE FOR COPD group-based self-management programme

Participants in the intervention group receive a SPACE for COPD(C) manual and are asked to attend the SPACE for COPD(C) group-based self-management programme usually within 1 month of their baseline appointment. The aim of the SPACE for COPD(C) programme is to support people with COPD in managing day-to-day tasks, minimise symptom burden, provoke health enhancing behaviour change and enhance emotional well-being. The programme is structured around the SPACE for COPD(C) manual, which combines both generic self-management skills and disease-specific tasks. The programme is facilitated by two trained HCPs (eg, physiotherapists, respiratory specialist nurses, occupational therapists and health psychologists) to groups of up to 10 participants and delivered through six 2-hour sessions, over a 5-month period. These sessions will be held at community venues, at times and locations to suit participants of the group to increase retention. Participants are liaised with in regards to preferences on timings and location of the group sessions to increase retention and engagement in the intervention. The content of the programme and accompanying self-management components^15^ are presented in tables 1 and 2. Participants are provided with a contact number for at least one of the facilitators throughout the course of the programme in case they have any further queries/are unable to attend any sessions.

**Table 1 T1:** SPACE for COPD(C) self-management programme session outline

Session 1 (week 1)	Introduction to SPACE for COPD(C)
1	Welcome and introductions
2	Group responsibilities
3	What does it mean to have COPD?
4	What is self-management?
5	How to use the SPACE for COPD(C) manual
6	Goal setting
7	Home activities for next session
8	Summary and close
Session 2 (week 2)	Introducing exercise and managing shortness of breath
1	Welcome back
2	Solution focused goal feedback
3	Managing shortness of breath
4	Introduction to the walking programme
5	Goal setting
6	Activities for next session
7	Summary and close
Session 3 (week 4)	Continuing exercise and saving energy
1	Welcome back
2	Solution focused goal feedback
3	Saving your energy
4	Strength training
5	Goal setting
6	Home activities for next session
7	Group discussion
8	Summary and close
Session 4 (week 8)	Managing stress and emotions and the COPD action plan
1	Welcome back
2	Solution focused goal feedback
3	Managing stress and emotions
4	Action plans

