### Data analysis

#### Study power

The power calculation was based on the primary outcome at 6 months.^30 31^ To detect a mean±SD between-group difference of 2.5±5.0 in the change in CAT with 80% power, 60 people per group are required (α=0.05, two tailed). In anticipation of a possible 25% attrition rate, the total sample size was increased to 75 per group (150 in total).

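### The intervention is delivered in groups, but the power calculation and the example tests treat patients as independent; with any positive within-group correlation, intervals are too narrow and type I error exceeds 5%

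*Protocol article*

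**What the plan says.** All references are to the Protocol article.

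- **Randomisation:** "Individuals are randomised (1:1) to the control group or the intervention". The unit is the patient.
- **Usual care (control group):** controls continue their ordinary reviews. Nothing is delivered to them in groups.
- **SPACE for COPD group-based self-management programme:** two trained professionals deliver the programme "to groups of up to 10 participants and delivered through six 2-hour sessions, over a 5-month period". Times and venues are chosen to suit the members of each group. Intervention fidelity adds that eight facilitators are trained in total.
- **Introduction:** group delivery is justified by social learning: "Peer support and use of other patients as role models are approaches grounded in this theory". The early sessions are spaced closely so that the group can become cohesive.
- **Study power:** "To detect a mean±SD between-group difference of 2.5±5.0 in the change in CAT" with 80% power, "60 people per group are required". This is raised to 75 per group for 25% attrition. No ICC, group size or design effect appears.
- **Quantitative analysis:** appropriate parametric and non-parametric methods will be used, with "within and between measures t-tests and analyses of variance" given as examples. No term for self-management group or facilitator is mentioned.

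**The concern.** This is a partially nested design: outcomes may be correlated within self-management groups in the intervention arm, while control patients remain independent. Members of a group share sessions, peers, venue and a pair of facilitators for five months, and the protocol intends them to influence one another.

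A t-test or ordinary analysis of variance estimates the variance of the intervention mean as though each patient contributed independent information. With positive within-group correlation that variance is larger than estimated. The confidence interval for the CAT difference is then too narrow, the null hypothesis is rejected too often when there is no effect, and the power available to a valid test is below the figure from the independent-patients formula. The error bears on the primary comparison and makes a spurious finding of benefit more likely.

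**Working it through.** **Inputs from the documents:** difference 2.5, SD 5.0, two-sided alpha 0.05, power 80%, 60 analysed and 75 enrolled per arm (Study power); groups of up to 10, intervention arm only (programme section).

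**Assumptions:** ICC 0.01 to 0.05, with 0.10 as an extreme; equal group sizes; the same total variance in both arms. The documents give no ICC. Enrolling 75 in groups of at most 10 needs at least 8 groups, so 60 analysed patients are at most 60/8 = 7.5 per group on average. Smaller groups are covered by m = 5 (12 groups). m = 10 (6 groups) is an upper bound.

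**Step 1: the plan's own figure.** n per arm = 2 × (5.0 × (1.960 + 0.842) / 2.5)² = 62.8, so 63; the exact t-test gives 64. The stated 60 is 3 to 4 short. With 60 per arm, SE = 5 × √(2/60) = 0.913 and power = Φ(2.5/0.913 − 1.96) = 78.2%. The stated figure is therefore close to a plain independent-patients calculation and has no margin to absorb a design effect. The shortfall from 80% to 78% is a separate matter.

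**Step 2: effect of grouping in one arm.**

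- Design effect in the intervention arm: DE = 1 + (m − 1) × ICC
- True SE of the difference: 5 × √((1 + DE)/60)
- Ratio of true to unadjusted SE: r = √((1 + DE)/2)
- Type I error of the unadjusted test: 2 × (1 − Φ(1.96/r))
- Power of a test using the true SE: Φ(2.5/SE − 1.96)

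Example, m = 7.5 and ICC 0.05: DE = 1 + 6.5 × 0.05 = 1.325; r = √(2.325/2) = 1.078; type I error = 2 × (1 − Φ(1.818)) = 6.9%; SE = 5 × √(2.325/60) = 0.984; power = Φ(2.540 − 1.96) = 72%.

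| Analysed per group (m) | ICC | True/unadjusted SE | Type I error | Power, 60 per arm |
|---|---|---|---|---|
| any | 0 | 1.000 | 5.0% | 78% |
| 5 | 0.01 | 1.010 | 5.2% | 77% |
| 5 | 0.02 | 1.020 | 5.5% | 77% |
| 5 | 0.05 | 1.049 | 6.2% | 74% |
| 7.5 | 0.01 | 1.016 | 5.4% | 77% |
| 7.5 | 0.02 | 1.032 | 5.7% | 76% |
| 7.5 | 0.05 | 1.078 | 6.9% | 72% |
| 10 (upper bound) | 0.05 | 1.107 | 7.7% | 70% |
| 10 (upper bound) | 0.10 | 1.204 | 10.4% | 62% |

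**Step 3: check by simulation.** The ordinary t-test was simulated with 40,000 runs per scenario. For groups of 7 and 8 (mean 7.5) it rejected in 5.3%, 5.7% and 6.9% of runs at ICC 0.01, 0.02 and 0.05. For groups of 10 it rejected in 7.5% at ICC 0.05 and 10.3% at 0.10. The formula is adequate here.

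**The case against.** - **The tests are only examples.** The list is introduced with an eg, the same section promises baseline adjustment and imputation, and an analysis plan that is not shown could include a group term. This stands. A reader might infer that the primary analysis is fixed as an unadjusted t-test; the article does not say so. But every method it names assumes independence, and the sample size is set in this document on that assumption whatever the analysis plan says.
- **The inflation is conditional.** A reader might infer that type I error is known to exceed 5%. It does so only if the ICC is positive and the grouping is ignored. The Introduction makes positive correlation plausible but says nothing about its size for change in CAT. At ICC 0.01 to 0.02 with 5 to 7.5 per group, the error is 5.2% to 5.7%, which is minor.
- **The largest figures need full groups.** Ten analysed patients in every group means every group at its maximum with no loss. The protocol says up to 10, plans for 25% attrition, and allows focus groups as small as 3. The m = 10 rows are therefore a bound, not an expectation.
- **Power.** A reader might attribute the whole fall from 80% to 72% to clustering. About 2 points are already lost at 60 per arm with independent patients; clustering accounts for about 6.
- **Severity.** The trial also has feasibility and acceptability aims, and the article reports recruitment in the past tense, so for the sample size only a restatement is practical. This lowers the urgency but does not make an analysis that ignores the grouping valid.

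**Conclusion.** The concern holds in conditional form and should be fixed. No section accounts for the grouping of the intervention arm. For any positive ICC, an analysis with the tests given as examples yields intervals that are too narrow.

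At ICC 0.01 to 0.05 with 7.5 analysed per group, the true SE is about 2% to 8% larger than the unadjusted one. Over 5 to 7.5 per group, type I error is about 5.2% to 6.9%. The upper bound with full groups is about 7.7% at ICC 0.05 and 10.4% at 0.10. The direction is secure given positive correlation; the size rests on an assumed ICC. Because only one arm is grouped, the variance inflation is (1 + DE)/2; applying the full design effect to the comparison would overstate the problem. Any further correlation from facilitators shared across groups is not counted here.

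**What to change.** 1. Analyse CAT and the other continuous outcomes with a partially nested linear mixed model: a random intercept for self-management group in the intervention arm only, separate residual variances by arm, and Satterthwaite or Kenward-Roger degrees of freedom.
2. Define the cluster as the group to which the patient was allocated, whether or not sessions were attended. The section on intervention adherence already compares attendance with the numbers allocated to each group, so the information is available.
3. Report the estimated ICC with its interval.
4. Restate the power in the Study power section over ICC 0.01 to 0.05 with the expected analysed group size. No additional enrolment is proposed.

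The cost is analysis-plan wording and one mixed model. Intervals become slightly wider and the stated power lower. With about eight groups the ICC will be estimated imprecisely, which is why the small-sample degrees of freedom are needed.

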**Methods and analysis:**

A prospective, multi-site, single-blinded randomised controlled trial (RCT) will be conducted, with follow-up at 6 and 9 months. Participants will be randomly assigned to either the control group (usual care) or intervention group (a six-session, group-based SPACE for COPD(C)self-management programme delivered over 5 months). The primary outcome is change in COPD assessment test at 6 months.

A discussion session will be conducted with HCPs who deliver the intervention to discuss and gain insight into any potential facilitators/barriers to implementing the intervention in practice. Furthermore, we will conduct semi-structured focus groups with intervention participants to understand feasibility and acceptability. All qualitative data will be analysed thematically.

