### Primary outcome

The primary outcome is health status, as measured by the COPD Assessment Test (CAT)^16^ at 6 months post-baseline. This measure was chosen due to ease of use in clinical practice compared with the Chronic Respiratory Questionnaire (as used in the previous RCT). The CAT is a validated, short (eight items) and simple patient completed questionnaire and assesses globally the impact of COPD (cough, sputum, dyspnoea and chest tightness) on health status. The CAT is scored 0–5 with a range of 0–40; scores of 0–10, 11–20, 21–30, 31–40 represent mild, moderate, severe or very severe clinical impact, respectively.

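### Observed normality chooses the test and observed baseline differences choose the covariates, so the primary model depends on the data and gives up precision that a fixed ANCOVA on baseline CAT would keep

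*Protocol article*

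**What the plan says.** Two rules stand in the Quantitative analysis section of the protocol article.

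- Choice of test: "Data will be checked for normality and appropriate parametric and non-parametric tests will be used". The examples offered are t-tests, within and between, and analyses of variance.
- Choice of covariates: "Any baseline differences will be adjusted for". No covariate is named, and nothing says what counts as a difference.

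The scale of the primary outcome varies. The abstract states "The primary outcome is change in COPD assessment test at 6 months", and Study power also works with a "between-group difference of 2.5±5.0 in the change in CAT". The Primary outcome section instead describes health status on the CAT at 6 months after baseline. Table 3 shows CAT collected at baseline, 6 months and 9 months.

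**The concern.** Under randomisation, imbalance in a variable measured before allocation is due to chance. It says nothing about whether that variable predicts outcome, so it is a poor reason to include or exclude a covariate. Baseline CAT is the natural predictor of 6-month CAT, and a rule triggered by imbalance drops it in most trials. A normality check that switches between a mean comparison and a rank test also changes the quantity being estimated, not only the test.

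Because neither rule has a threshold, several defensible primary analyses remain open after the data are seen. The two wordings of the outcome add to this. Under a t-test, change and 6-month value are different estimators with different precision. At stake are power that the collected data could supply, and a primary result that does not depend on decisions made with the data in hand.

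**Working it through.** **Inputs from Study power.** Difference 2.5 and SD of change 5.0; "α=0.05, two tailed"; 80% power; "60 people per group are required"; 75 per group recruited against 25% attrition.

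**The plan's own figure.** n = 2(1.960 + 0.842)² × 5.0²/2.5² = 62.8, so 63 per group (64 with the t distribution). The stated 60 gives 78.2% power (normal) or 77.5% (t). A 25% loss from 75 leaves 75 × 0.75 = 56.25, about 56 per group, with 74.6% power (t) on change scores. The shortfall in sample size is a separate point. It matters here because the design has no power to spare.

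**Assumptions.** The baseline to 6-month correlation ρ is not in the article, so I show a range from 0.5 to 0.9. I also assume equal variance σ² at both visits and independent participants, that is, no allowance for clustering within intervention groups.

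**Formulas.**

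- Change score: Var = 2σ²(1 − ρ) = 25, so σ² = 25/[2(1 − ρ)].
- ANCOVA: residual Var = σ²(1 − ρ²) = 25(1 + ρ)/2, so SD = 5√[(1 + ρ)/2].
- 6-month score alone: SD = σ = 5/√[2(1 − ρ)].

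The ANCOVA to change-score variance ratio is (1 + ρ)/2, which is below 1 for every ρ below 1. The direction is therefore certain under equal variances, and only the size depends on ρ.

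**Power at 56 per group (noncentral t).**

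| ρ | ANCOVA SD | ANCOVA | Change-score t-test | 6-month t-test |
|---|---|---|---|---|
| 0.5 | 4.33 | 85.7% | 74.6% | 74.6% |
| 0.6 | 4.47 | 83.5% | 74.6% | 65.0% |
| 0.7 | 4.61 | 81.2% | 74.6% | 52.9% |
| 0.8 | 4.74 | 78.9% | 74.6% | 38.2% |
| 0.9 | 4.87 | 76.8% | 74.6% | not tabulated |

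ANCOVA reaches 80% only for ρ up to about 0.75 (80.1% at 0.75, 79.8% at 0.76).

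**The conditional rule by simulation.** 10,000 runs, 60 per group, normal data, with ANCOVA used only if baseline CAT differs at p < 0.05. That threshold is my assumption, since the article gives none.

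| Quantity | ρ = 0.5 | ρ = 0.7 |
|---|---|---|
| Power, fixed ANCOVA | 87.8% | 84.4% |
| Power, conditional rule, change score otherwise | 79.1% | 78.7% |
| Power, conditional rule, 6-month score otherwise | 78.6% | 57.3% |
| Type I error, conditional rule, change score otherwise | 4.5% | 4.8% |
| Type I error, conditional rule, 6-month score otherwise | 4.2% | 3.5% |
| Type I error, best of change, 6-month score and ANCOVA | 9.7% | 10.1% |

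The simulation did not cover the normality-driven switch to a rank test.

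**The case against.** **The model belongs in an analysis plan that is not shown.** This is a journal article, and the absence of a named ANCOVA is not itself a fault. That stands. What remains is that the article states two selection rules, and those are what need correcting, even if a later plan overrides them. The word only is not in the covariate sentence, but adjusting for what differs is its natural reading.

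**The false-positive rate is not shown to rise.** A reader might infer that a data-dependent model inflates type I error. The simulation does not support this for the covariate rule applied mechanically: the rate stayed between 3.5% and 4.8%. The figure of about 10% needs an analyst who picks the most favourable of three analyses, which the article does not propose. It shows what the open choice permits, not what is planned.

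**The gain rests on assumed quantities.** Correct. At ρ = 0.9 it is only about 2 points. A reader might conclude that ANCOVA repairs the sample size, but that fails above ρ of about 0.75 and ignores clustering. Nor does the article name a change-score t-test as the primary test. It is used here as the comparator because Study power is built on change.

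**Within-arm tests.** They are listed among examples for all quantitative data. Nothing says they will serve as evidence of efficacy, so that charge is not made.

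**Baseline CAT may not be pre-allocation.** This is the most serious objection. Table 3 lists the questionnaires after randomisation, with an unblinded team member. The Randomisation section places randomisation after consent and spirometry, with allocation disclosed at once. If the table order is the visit order, baseline CAT is self-reported with allocation known, and imbalance in it need not be chance. This qualifies the remedy. It does not favour change scores: they subtract baseline CAT in full, whereas ANCOVA under equal variances subtracts it with slope ρ.

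**Conclusion.** The point holds as one of efficiency and prespecification. As written, the rules leave the primary model to the data and, read literally, omit baseline CAT when it is balanced. At 56 evaluable per group a fixed ANCOVA gains about 11 points of power at ρ = 0.5, between 6 and 7 at 0.7, about 4 at 0.8 and about 2 at 0.9 over a change-score t-test. This assumes an SD of change of 5.0, equal variances and no clustering. If the 6-month wording were followed with an unadjusted t-test, the loss would be much larger for ρ above 0.5. Type I error inflation from the mechanical covariate rule is not shown, and full recovery of 80% power cannot be promised. The point should be corrected, but it does not invalidate the trial.

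**What to change.** 1. Prespecify one primary model: 6-month CAT on randomised arm and baseline CAT, fitted whatever the normality or balance checks show, reporting the adjusted mean difference with 95% CI. With baseline CAT in the model, change and 6-month value give the same treatment effect, so the two outcome wordings are reconciled.
2. Delete the sentence "Any baseline differences will be adjusted for" and make rank-based tests a sensitivity analysis.
3. Use the same form for continuous secondary outcomes that have a baseline value in both arms. Table 3 appears to limit baseline shuttle tests to the intervention arm, so this cannot be promised for exercise capacity until that entry is clarified.
4. Confirm whether baseline CAT is completed before allocation is disclosed. If it was not, state this as a limitation of the adjusted estimate and report an unadjusted 6-month comparison as a sensitivity analysis.

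Items 1 to 3 cost wording only, since baseline CAT is already collected. Item 4 costs a check of the visit procedure. If CAT did follow disclosure, wording cannot repair that, and the article reports recruitment in the past tense, so the visit order may no longer be changeable.
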